## Abstract

**Background:**

Chronic subdural haematoma (CSDH) is a common condition in the elderly that often requires neurosurgical management. For small CSDH, evidence has emerged that statins may reduce haematoma volume and improve outcomes, presumably by reducing local inflammation and promoting vascular repair. We wish to extend this evidence in a study that aims to determine the efficacy and safety of atorvastatin combined with low-dose dexamethasone in patients with CSDH.

**Methods:**

The second ATorvastatin On Chronic subdural Hematoma (ATOCH-II) study is a multi-centre, randomized, placebo-controlled, double-blind trial which aims to enrol 240 adult patients with a conservative therapeutic indication for CSDH, randomly allocated to standard treatment with atorvastatin 20 mg combined with low-dose dexamethasone (or matching placebos) daily for 28 days, and with 152 days of follow-up. The primary outcome is a composite good outcome defined by any reduction from baseline in haematoma volume and survival free of surgery at 28 days. Secondary outcomes include functional outcome on the modified Rankin scale (mRS) and modified Barthel Index at 28 days, surgical transition and reduction in haematoma volumes at 14, 28 and 90 days.

**Discussion:**

This multi-centre clinical trial aims to provide high-quality evidence on the efficacy and safety of the combined treatment of atorvastatin and low-dose dexamethasone to reduce inflammation and enhance angiogenesis in CSDH.

**Trial registration:**

ChiCTR, ChiCTR1900021659. Registered on 3 March 2019, http://www.chictr.org.cn/showproj.aspx?proj=36157.

**Supplementary Information:**

The online version contains supplementary material available at 10.1186/s13063-021-05871-9.

## Administrative information

Note: the numbers in curly brackets in this protocol refer to SPIRIT checklist item numbers. The order of the items has been modified to group similar items (see http://www.equator-network.org/reporting-guidelines/spirit-2727-statement-defining-standard-protocol-items-for-clinical-trials/).

## Introduction

### Background and rationale {6a}

Chronic subdural haematoma (CSDH) represents one of the most common forms of intracranial haemorrhage, causing a variety of diagnostic and therapeutic challenges as rates increase in ageing populations and increased use of antithrombotic agents [1, 2]. Evacuation of CSDH through twist-drill or bur-hole craniotomy remains the main form of treatment for symptomatic patients [3], but surgery is associated with high risks of operative complications and recurrence [4]. Non-surgical options include the use of mannitol, glucocorticoids, angiotensin-converting enzyme inhibitors, tranexamic acid and platelet-activating factor receptor inhibitor, but none has been shown to be clearly effective [5–8].

Impaired angiogenesis and inflammation of the surrounding neomembrane may be important in the pathophysiology of CSDH, promoting the slow expansion of blood from immature ‘leaky’ vessels after trauma [7, 9]. The pleiotropic effects of statins on inflammation and endothelial progenitor cell activity [10–14], which may promote haematoma reabsorption, were recently tested in the ATorvastatin On Chronic subdural Hematoma (ATOCH) study, a multi-centre double-blind placebo-controlled randomized trial in China [15]. The positive results of atorvastatin 20 mg daily significantly reduced haematoma volume, and improving clinical outcomes [15] has had a major impact on clinical practice in China, with this medical treatment being widely adopted for both primary conservative and adjunctive post-surgical management of CSDH [16, 17]. However, additional strategies are warranted, as response to atorvastatin is slow in many patients and ineffective over several weeks of treatment in 10% of patients [15]. Moreover, any benefits of atorvastatin at a high dose may be offset by adverse effects, such as intracranial haemorrhage [18], and may not have any greater efficacy than at low dose [13]. Dexamethasone had shown some effect on CSDH, but it is also complicated by adverse effects, particularly at high doses [19–22]. We therefore initiated the second Atorvastatin combined with dexamethasone in Chronic subdural Haematoma (ATOCH-II) trial to determine the efficacy and safety of dexamethasone combined with low-dose atorvastatin in patients with CSDH.

### Objectives {7}

#### Hypothesis

The combination of low-dose atorvastatin and low-dose dexamethasone is superior to low-dose atorvastatin alone on the outcome of treatment for patients with chronic subdural haematoma.

#### Research question

The primary aim of ATOCH-II is to determine whether the combination of low-dose atorvastatin and low-dose dexamethasone is superior to low-dose atorvastatin alone on the composite outcome of haematoma volume, transition to surgery and death at 28 days in patients with CSDH.

### Trial design {8}

ATOCH-II is a multi-centre, prospective, double-blind, placebo-controlled, randomized trial involving 240 CSDH patients with a conservative therapeutic indication for CSDH, randomly allocated to standard treatment with atorvastatin 20 mg combined with low-dose dexamethasone (or matching placebos) daily for 28 days, and with 152 days of follow-up. The demographic information of patients enrolled at each study site was imported into the central randomization system, which then generated a random number that determined whether a patient received atorvastatin or placebo at a randomization ratio of 1:1. There was no stratification during the randomization.

## Methods: participants, interventions and outcomes

### Study setting {9}

ATOCH-II trial recruited patients from 14 neurosurgery centres in China who are collaborative partners in the Oriental Neurosurgical Evidence-based Study Team (ONET). ONET is the first neurosurgical professional organization devoted to evidence-based medicine in China (Chair, Department of Neurosurgery, Tianjin Medical University General Hospital) with the mission to establish clinical research thinking, train clinical researchers, conduct randomized trials and promote the development of evidence-based medicine in neurosurgery.

### Eligibility criteria {10}

The study population will be drawn from consecutive patients with CSDH admitted to ONET neurosurgical centres. Patients are eligible who meet all of the following inclusion criteria: age ≥ 18 and ≤ 90 years; diagnosis of supratentorial (unilateral or bilateral) CSDH confirmed on CT imaging within 72 h after admission; a single unilateral haematoma ≥ 10 mL; pre-morbid functional independence, estimated according to scores 1 (no symptoms), 2 (symptoms) or 3 (some disability but independent in function) on the modified Rankin scale (mRS); the attending physician’s judgement that cerebral herniation and/or surgical evacuation are unlikely to occur; and the provision of informed consent or by an appropriate proxy according to local requirements.

The exclusion criteria include the following: known allergy to a statin (< 4 weeks), glucocorticoid or their ingredients; considered to have a high likelihood of cerebral trauma or cerebral herniation and/or requirement surgical evacuation or decompression; structural lesions including tumour, haematologic diseases, tuberculous, arachnoid cyst, vascular malformation, ventricular peritoneal shunt or other severe co-morbidity; abnormal liver function, hepatitis or uncontrolled liver disease, as well as other disease that has an influence of prognosis or the ability to assess the study outcomes; uncontrolled diabetes mellitus, with blood glucose levels consistently > 10 mmol/L; history of femoral head necrosis; recent (< 4 weeks) corticosteroid or anticoagulation use or abnormal coagulation function (< 4 weeks); likelihood of pregnancy or breastfeeding during the course of the study; participation in another clinical trial (< 4 weeks); high likelihood of poor adherence to the treatment or follow-up schedule; and any other reason according to the opinion of the attending clinician researcher.

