#### Intervention description {11a}

All patients are to take oral 20 mg atorvastatin (one tablet) daily for 4 weeks as a standard of care. Those patients allocated to the intervention group will receive extra dexamethasone with a dose of 0.75 mg per once for three times daily during the first 14 days, and thereafter, the dose will be reduced to twice daily for 7 days, and then once a day for another 7 days. Thus, a total of 560 mg atorvastatin and 47.25 mg dexamethasone will be taken for 28 days. Patients assigned to the control group will receive the same open atorvastatin regimen but also placebo dexamethasone in the same schedule over 28 days.

At the end of the 28-day treatment period, haematoma volume will be re-evaluated on repeat CT scans and the following treatment regimens considered: (i) if the haematoma has resolved or present in a very small amount, the investigator can stop study treatment and only conduct follow-up observations until 180 days; (ii) if the haematoma appears reduced but still present, the investigator can decide either to consider ceasing medication and observing considering early surgery; (iii) if there is no obvious change in the haematoma, two researchers can jointly determine whether to continue conservative management or undertake surgery; and (iv) if the amount of haematoma is increased, the patient may undergo surgery.

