### Outcomes {12}

The primary outcome is a composite of ‘good outcome’, including any reduction in subdural haematoma volume from baseline and free of surgery and death within 28 days of the treatment. The haematoma volume is measured centrally using the Tada formula of maximal length (L) × maximal width (W) × maximal thickness (H), divided by 2 [23], on the acquired CT images by 3 independent neuroradiologists blind to the treatment location. Details of the location, density and compartment of the haematoma are also recorded.

Secondary outcomes include functional outcome according to a ‘shift’ in the distribution of the full range of scores on mRS at 28 days; function on the modified Barthel Index measure of actives of daily living (ADL-BI) at 28 days; surgical intervention at 28, 90 and 180 days; and reduction in haematoma volume at 14, 28 and 90 days.

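### Two eligibility rules are wrong or ambiguous as written: a 4-week limit is attached to statin allergy, and the mRS numbers do not match their printed descriptors

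*Protocol article*

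**What the plan says.** Both rules stand in the protocol article under Eligibility criteria {10}.

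- **Inclusion.** The aim is given as "pre-morbid functional independence, estimated according to scores" on the modified Rankin scale (mRS), and the admissible values are "scores 1 (no symptoms), 2 (symptoms) or 3 (some disability but independent in function".
- **Exclusion.** The list opens with "known allergy to a statin (< 4 weeks), glucocorticoid or their ingredients". Further down, the same window appears as "recent (< 4 weeks) corticosteroid or anticoagulation use or abnormal coagulation function (< 4 weeks", and again for participation in another trial. The list ends with a discretionary exclusion, "any other reason according to the opinion of the attending clinician researcher".

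Two other sections bear on these rules. Intervention description {11a} says "All patients are to take oral 20 mg atorvastatin (one tablet) daily for 4 weeks as a standard of care", and the control group follows the same atorvastatin regimen. Outcomes {12} makes mRS a secondary outcome, analysed as a shift over the "distribution of the full range of scores on mRS at 28 days". Table 1 schedules mRS at screening and at days 28, 90 and 180.

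**The concern.** An eligibility rule should give one answer for each patient. These two do not.

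For mRS, the number and the words beside it point to different grades of the standard scale. A site that works from the digits selects different patients from a site that works from the words. For statin allergy, a time limit sits on something that is not normally time-limited, and it sits only on the statin half of the clause. Read literally, a long-known statin allergy is not a reason for exclusion in a trial where every participant takes a statin.

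At stake are consistent enrolment across the 14 centres, participant safety under the allergy rule and, more remotely, consistent coding of an instrument that is also a secondary outcome.

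**Working it through.** The plan gives no figure on this point, so the check sets the texts side by side.

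**Step 1: mRS numbers against descriptors.** The article does not print the mRS grades. The two right-hand columns rest on the standard 0–6 definition of the instrument.

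| Number printed | Descriptor printed (paraphrased) | Standard grade for that descriptor | Standard meaning of that number |
|---|---|---|---|
| 1 | symptom-free | 0 | symptoms, no significant disability |
| 2 | symptoms present | 1 | slight disability, independent |
| 3 | some disability, still independent | 2 | moderate disability, needs some help |

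Each number is its descriptor's standard grade plus one: 0 + 1 = 1, 1 + 1 = 2, 2 + 1 = 3.

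- Admitted by number: {1, 2, 3}.
- Admitted by descriptor: {0, 1, 2}.
- Admitted either way: {1, 2}.
- Different answers: grade 0 (admitted only by descriptor) and grade 3 (admitted only by number).

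The criterion's own purpose is functional independence. The descriptor set fits it. The number set leaves out symptom-free patients and lets in patients who need help. No other section defines a scale that starts at 1.

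**Step 2: the 4-week window.** It appears four times in the exclusion list.

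| What it qualifies | Kind of item |
|---|---|
| statin allergy | a standing hypersensitivity |
| corticosteroid or anticoagulant use | recent exposure |
| abnormal coagulation | recent state |
| another clinical trial | recent exposure |

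Three of the four uses qualify something recent. The allergy use is the exception, and the glucocorticoid part of the same clause carries no window. Set beside Intervention description {11a}, where all patients take atorvastatin, the literal rule leaves a patient with an older known statin allergy outside this exclusion. No other listed criterion requires that patient to be excluded.

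**Step 3: reach into the analysis.**

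- The primary outcome in Outcomes {12} consists of haematoma volume, surgery and death. It contains no mRS.
- The adjusted primary model in Statistical methods {20a} uses site, age, sex and baseline haematoma volume. mRS is not among them.
- The subgroups in {20b} are haematoma volume and age.
- The sample size in {14} rests on good-outcome rates, a 20% absolute difference and 5% loss to follow-up. Neither rule enters it.
- The mRS shift at 28 days is analysed by ordinal logistic regression, which uses only the order of the categories. If every record were one step too high, the treatment comparison would not change. Only a mixture of codings would matter.

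**The case against.** The strongest reply is that these are slips of wording that no sensible site would follow.

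- **mRS.** Every number has a descriptor beside it, the sentence begins with the aim of independence, and all three descriptors fit that aim. Misselection needs a site or form that uses the bare digits. This stands as a limit on likelihood, but a rule that gives two answers still needs correcting. It is also true that this half relies on the standard grade definitions and not on a contradiction printed in the article.
- **Allergy.** The clause goes on to ingredients without a time limit, which could be read to cover the statin, and the closing discretionary exclusion lets a clinician refuse such a patient. Both are fair, but the first only adds another reading, and the second permits exclusion without requiring it.
- **Article versus full protocol.** The article condenses a protocol that is not shown, and the slips may exist only in the article. This stands, and it decides how far the remedy should go.

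A reader might infer more than the document supports:

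- *That baseline adjustment is corrupted.* mRS is not an adjustment covariate.
- *That the shift analysis is compromised by sites coding differently.* Nothing shows 1-based scoring at any visit. Data go into one electronic capture system with central checks, and allocation is masked, so such an error would not be expected to favour an arm. It is worth a check, not a finding.
- *That the 141 patients reported under Trial status were enrolled under this wording.* That section says enrolment began with version 1.5, whose text is not shown.
- *That the 4-week limit strayed from a lost criterion on recent statin use.* The list has no such criterion, but nothing shows that one was intended.

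**Conclusion.** The point holds as a defect of two operative eligibility rules. The allergy defect shows from the article alone: a time limit on an allergy, in a trial where all participants receive the drug class concerned. The mRS defect holds given the standard 0–6 grades: numbers and descriptors differ by one grade throughout, the two readings disagree at grades 0 and 3, and only the descriptors fit the stated aim.

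The size cannot be estimated. The document gives neither the pre-morbid mRS distribution nor the frequency of statin allergy, and it does not show which reading sites used. Power and the primary analysis method are unaffected. Correction is still worthwhile because it concerns participant safety and uniform enrolment, and because recruitment was continuing at the reported date: 141 of 240 enrolled, so 240 − 141 = 99 still to come.

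**What to change.** 1. The investigators reconcile what the 4-week limit in the allergy clause refers to, and reissue that exclusion so that it has one reading. The clinical content is for them to decide.
2. Align the mRS numbers in the inclusion criterion with the printed descriptors, using a single stated scale.
3. Compare both rules with protocol version 1.5 and the electronic case report form. Confirm in the same check that one mRS coding is used at screening and at days 28, 90 and 180. Do this before unblinding.
4. If the wording exists only in the article, correct the article and stop there. If it was in operational use, review enrolled patients against the corrected text, log any deviations, and keep those patients in the intention-to-treat analysis.

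The cost is a clarification letter and a form check, with no new data collection. The downside is possibly a few logged deviations.

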### Consent process {26a}

Each participating site must obtain written approval(s) from their hospital research ethics committee (EC) (e.g. institutional review board [IRB]) and any other relevant regional or national body, before patient recruitment commences. For recruitment, each patient or guardian, assisted by a nurse coordinator assigned to the study, completed a short questionnaire about his or her condition, underwent physical exams by an attending neurosurgeon who was blinded to the treatment and received a CT scan. All data were collected on-site by nurse coordinators and submitted electronically to the Data Acquisition System, which also randomized the patients. All ethical and legal requirements are required to be met before any subject is enrolled in the trial. Written informed consent was obtained by the doctor from each participant or his/her legal surrogate.

### Additional consent provisions for collection and use of participant data and biological specimens {26b}

The study consent process includes permission for additional analysis of the collected data for systematic reviews and individual patient data pooling projects. Peripheral blood tests will be collected regularly to assess the health status of patients and to evaluate the safety of drug use. The protocol has been approved by the Research and Ethics Committee of the IMSS (CNIC registry number: IRB2018-088-01). The procedures are in compliance with the SPIRIT guidelines and letter of the Declaration of Helsinki, the conditions and principles of GCP, applicable local regulatory requirements and laws. Before enrolment, patients or their family guardians are fully informed of the trial, its potential outcomes and adverse events and are to provide informed consent.

### Interventions

#### Explanation of the choice of comparators {6b}

The positive results of atorvastatin 20 mg daily significantly reduced haematoma volume, and improving clinical outcomes has had a major impact on clinical practice in China. However, additional strategies are warranted, as response to atorvastatin is slow in many patients and ineffective over several weeks of treatment in 10% of patients. Dexamethasone had shown some effect on CSDH, but it is also complicated by adverse effects, particularly at high doses. We therefore initiated the second Atorvastatin combined with dexamethasone in Chronic subdural Haematoma (ATOCH-II) trial to determine the efficacy and safety of dexamethasone combined with low-dose atorvastatin in patients with CSDH.

#### Intervention description {11a}

All patients are to take oral 20 mg atorvastatin (one tablet) daily for 4 weeks as a standard of care. Those patients allocated to the intervention group will receive extra dexamethasone with a dose of 0.75 mg per once for three times daily during the first 14 days, and thereafter, the dose will be reduced to twice daily for 7 days, and then once a day for another 7 days. Thus, a total of 560 mg atorvastatin and 47.25 mg dexamethasone will be taken for 28 days. Patients assigned to the control group will receive the same open atorvastatin regimen but also placebo dexamethasone in the same schedule over 28 days.

At the end of the 28-day treatment period, haematoma volume will be re-evaluated on repeat CT scans and the following treatment regimens considered: (i) if the haematoma has resolved or present in a very small amount, the investigator can stop study treatment and only conduct follow-up observations until 180 days; (ii) if the haematoma appears reduced but still present, the investigator can decide either to consider ceasing medication and observing considering early surgery; (iii) if there is no obvious change in the haematoma, two researchers can jointly determine whether to continue conservative management or undertake surgery; and (iv) if the amount of haematoma is increased, the patient may undergo surgery.

#### Criteria for discontinuing or modifying allocated interventions {11b}

Eligible patients are centrally randomized in a 1:1 allocation ratio to intervention (atorvastatin combined with low-dose dexamethasone) and control (atorvastatin combined with matching placebo) groups using a blocked randomization method via a data acquisition system for electronic data capture (DAS for EDC, version 5.0) developed by Stemexcel Technology Co. Ltd., Beijing.

If a participant develops any form of neurological deterioration (e.g. altered level of consciousness) that is suggestive of expansion of the haematoma, they may be admitted to the hospital for assessment and treatment until their symptoms are relieved or resolve. If surgery is undertaken for a deteriorating patient, the randomized oral study medication is to be resumed as soon as possible after the operation until the end of the planned 28-day treatment period.

The patient has the right to refuse treatment at any time or to withdraw completely from the trial. The investigator can also ask the patient to withdraw from the trial, including (1) the compliance of the subjects was poor and the scheme was violated, (2) unacceptable adverse reactions/serious adverse events occur, (3) subjects experienced serious complications during the trial and urgent measures were required, (4) the subject withdraws from the clinical trial or withdraws the informed consent form and (5) other special circumstances.

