## Statistics methods

### Statistical methods for primary and secondary outcomes {20a}

The primary analysis will be performed according to the intention-to-treat (ITT) principle, comprising all randomized participants. A per-protocol analysis will also be undertaken for all participants who have taken at least one dose of the trial medication and complete at least one follow-up assessment. The description of indicators will be by number of cases (and percentages) for categorical variables, and mean (standard deviation) or median (interquartile range) for continuous variables. The chi-square test and logistic regression with adjustment for site, age, sex and baseline haematoma volume will be adopted for the comparison of the primary outcome between the treatment groups. For secondary outcomes, Student’s *t*-test or non-parametric Wilcoxon tests will be performed for continuous outcomes and the chi-square test for dichotomous outcomes. Ordinal logistic regression will be used for the analysis of the shift in the full range of scores on the mRS. All statistical tests are two-sided, with a *p*-value < 0.05 indicating statistical significance. All analysis will be conducted using SAS 9.4 (SAS Institute Inc., USA).

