### SAE reporting and harms {22}

A serious adverse event (SAE) is defined as an event causing or with potential to cause significant harm or requiring medical intervention, whether or not it is considered related to the study treatment. A non-serious adverse event is defined as any undesirable medical experience occurring to a patient, including abnormal laboratory values without clinical consequences.

All SAEs are to be reported within 24 h of the site investigator becoming aware, and a full report is to be filled to the sponsor and the state food and drug administration (SFDA). The ethics committee of pharmaceutical affairs of ONET will conduct an investigation to confirm the causes of an SAE, decide whether the participant can continue with the study medication and deal with the related participants’ complications and adverse events. All patients are to be followed up according to the intention-to-treat principle. The SAE should be documented in the medical records or patient file and signed and dated by the investigator, for audit and monitoring. Safety outcomes are reported to the presiding Ethics Committees in line with their requirements every 6 months, as well as for review by the DMSB at each meeting.

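### Investigators may take patients out of the trial, not only off study drug, for post-randomisation events, which conflicts with following up and analysing everyone as randomised

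*Protocol article*

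**What the plan says.** All references are to the protocol article.

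- **Criteria for discontinuing or modifying allocated interventions {11b}.** For the patient, two different acts are named: "The patient has the right to refuse treatment at any time or to withdraw completely from the trial". For the investigator, only leaving the trial is named: "The investigator can also ask the patient to withdraw from the trial, including (1) the compliance of the subjects was poor". That item goes on to require that the protocol was also breached. The next two reasons are "2) unacceptable adverse reactions/serious adverse events occur, (3) subjects experienced serious complications during the trial and urgent measures were required". The list ends with the patient's own withdrawal and an open category for other circumstances.
- **The same section, on surgery for deterioration.** The patient stays on allocated treatment: "the randomized oral study medication is to be resumed as soon as possible after the operation until the end of the planned 28-day treatment period".
- **SAE reporting and harms {22}.** "All patients are to be followed up according to the intention-to-treat principle". After a serious adverse event, the ethics committee named there is to "decide whether the participant can continue with the study medication". The question is about the drug, not about membership of the trial.
- **Statistical methods {20a}.** "The primary analysis will be performed according to the intention-to-treat (ITT) principle, comprising all randomized participants".
- **Outcomes {12}.** A good outcome is "any reduction in subdural haematoma volume from baseline and free of surgery and death within 28 days of the treatment".
- **Missing data {20c}.** Missing 4-week data in the full analysis set are filled by last observation carried forward. Multiple imputation is a sensitivity analysis, used only if more than 5% of patients lack the primary outcome.

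**The concern.** Poor adherence with a protocol breach, adverse reactions and complications all occur after randomisation. They are related to prognosis, and dexamethasone may change how often they occur; the Background {6a} itself notes its adverse effects. A rule that lets a site end participation for these reasons lets data collection stop for a selected group, and that group may differ between arms.

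Two kinds of data are at risk. The first is the primary outcome, which needs a day-28 CT and knowledge of surgery and death up to that day. The second is the harms record to day 180, for the very patients whose harms prompted the withdrawal. No analysis plan can recover a scan that was not done or an event that was not recorded.

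**Working it through.** **1. The passages side by side.** A site that takes a patient out of the trial after a serious adverse event under {11b} cannot also follow that patient up by intention to treat under {22}. The primary analysis {20a} can still count the patient, but only by filling in an outcome that {11b} allowed to go uncollected. There is also a tension inside {11b}: a deterioration that leads to surgery keeps the patient on study drug, yet it may also fit the third withdrawal reason.

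**2. The plan's own figure.** Inputs from Sample size {14} and {20a}: control 62.6%, which is (48 + 20 + 9)/(81 + 30 + 12) = 77/123; difference 20 points, so 82.6%; power 90%; two-sided 5%; 5% loss.
- n per arm = [1.96·√(2·0.726·0.274) + 1.2816·√(0.626·0.374 + 0.826·0.174)]² / 0.20² = 102.4, so 103. With continuity correction it is 113.
- 113/0.95 = 118.9, so 119 per arm and 238 in total. The stated 240 is reproduced.
- Power by the uncorrected formula is 92.8% with 5% of both arms missing (114 per arm), 91.5% with 10% (108) and 89.9% with 15% (102). Power is therefore not the main issue; bias is.

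**3. Illustration with withdrawn patients left out.** Assumptions not in the documents: the true good-outcome rate is 62.6% in both arms, a fraction w is withdrawn, and the good-outcome rate among the withdrawn is q. The observed rate is (0.626 − w·q)/(1 − w).
- 10% against 5%, q = 20%: (0.626 − 0.020)/0.90 = 67.3% and (0.626 − 0.010)/0.95 = 64.8%, a difference of +2.5 points.
- 10% against 5%, q = 40%: 65.1% and 63.8%, a difference of +1.3 points.
- Two-sided rejection at nominal 5% is then 6.8% and 5.5%.
- 15% against 5%: +5.3 points (q = 20%) to +2.8 points (q = 40%), with rejection of 13.2% to 7.2%.
- Equal withdrawal in both arms, or q = 62.6%, gives no bias under the null.

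**4. What the planned carry-forward does.** Table 1 has CT at screening, day 14, day 28 and day 90.
- Withdrawal before the day-14 CT carries the baseline volume forward: no reduction, so a failure.
- Withdrawal after it carries the day-14 result forward, which may be a good outcome even if surgery or death follows unrecorded.

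Two extremes, with the same assumed 10% against 5% and q from 20% to 40%:
- All withdrawn scored as failures: the difference is −(0.10 − 0.05)·q, or −1.0 to −2.0 points.
- All withdrawn scored as good: (0.10 − 0.05)·(1 − q), or +4.0 to +3.0 points.

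The sign depends on when patients leave.

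**5. The imputation trigger.** 5% of 240 is 12 patients. At exactly the planned loss the condition of more than 5% is not met. At 10% against 5% (12 + 6 = 18, or 7.5%) it is met, but the imputation remains a sensitivity analysis and cannot observe the missing scan.

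**The case against.** The strongest reply is that this is loose wording. The heading of {11b} concerns interventions, withdrawal is discretionary, investigators are blinded {17a}, and {22} already says that all patients are followed up. An intention-to-treat analysis can include patients who withdraw. The article is also condensed, and the full protocol may set out data collection after withdrawal.

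Part of this stands. The authors may well have meant stopping study drug. But the sentence just before distinguishes refusing treatment from leaving the trial completely, and the investigator's list uses only the latter. This is a stated rule that contradicts another stated rule, not an omitted detail. Blinding does not stop a drug from causing the events that trigger withdrawal.

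Several stronger readings are tempting and are not supported:

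- **That missing outcomes will depend on treatment.** This is plausible, not certain, because withdrawal is discretionary.
- **That the bias favours dexamethasone.** Step 4 shows either sign is possible under the planned rule.
- **That poor compliance alone suffices.** The first reason also requires a protocol breach.
- **That operated patients are lost to the primary outcome.** Surgery or death within 28 days and before withdrawal already settles it as a failure.
- **That safety follow-up is definitely lost.** {22} points the other way, and the post-trial care section {30} provides hospital care for serious drug-related complications until symptoms resolve.
- **That the unknown outcomes outweigh the detectable effect.** If 10 and 5 patients were withdrawn, the unknown outcomes would span 10/120 + 5/120 = 12.5 points, against a critical difference of 1.96·√(2·0.726·0.274/120) = 11.3 points. That width is a worst-case bound on assumed counts, not an estimate of bias.

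**Conclusion.** The point holds as a conflict of text with a possible bias. As written, {11b} lets the investigator end trial participation for post-randomisation events, against the follow-up rule in {22} and to the detriment of the all-randomised analysis in {20a}. Carry-forward does not repair the loss, and multiple imputation is only a conditional sensitivity analysis.

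The size of any bias cannot be taken from the documents, which give no withdrawal rates by arm or reason. On assumed withdrawal of 10% against 5%, with no true effect and withdrawn patients left out, it is about 1 to 2.5 points. It is zero if withdrawal is balanced with equal outcome rates among the withdrawn in both arms, or if the withdrawn do as well as the rest. The conflict itself rests on no assumption beyond reading the words as they stand. The patient's own withdrawal of consent is legitimate and not part of the problem.

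**What to change.** Reconcile {11b} with {22} and {20a} by separating two things: the end of study treatment and the end of follow-up. The clinical criteria for stopping treatment need not change for this purpose and are for the sponsor. The overlap between resuming drug after surgery and the third withdrawal reason, and the question of who decides after a serious adverse event, should be made consistent in the same edit.

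Then state that every randomised patient who has not withdrawn consent stays in follow-up to day 180, with the Table 1 assessments (CT to day 90; surgery, mRS, ADL-BI and adverse events to day 180) and survival status recorded at the same contacts, and is analysed in the allocated group.

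**Cost.** A short amendment with the signatures and ethics approval that section {25} requires, and a notice to the 14 centres. No new visits are needed. Trial status gives 141 of 240 enrolled on 7 November 2021, so at that date the change would have covered the remaining 99 patients and those still in follow-up. It cannot recover data already lost.
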